### Participants

#### Eligibility criteria

The particular focus of this study, which aims to introduce a process of change in health promotion practice in PHC under a framework of participative research with health professionals, community partners and researchers, determines the two characteristics that define the participants: (1) the intervention unit is the PCC; and (2) the centre must be especially interested in health promotion. The creative work to be undertaken requires that the professionals and health centres be positively motivated with respect to changing risk behaviours of their patients and the integration of health promotion in daily practice. That is why the following factors were considered in order to identify the centres that were eligible: (1) previous history of participation or evaluation of programmes for health promotion in the last 10 years, (2) previous initiatives of preventive practice optimisation and the promotion of healthy lifestyles, (3) existence of programmes, resources, services or initiatives for health promotion in the community or geographical area of reference, (4) positive attitude to working together and cooperation between the professionals of the centre, (5) centres in which it would be possible to make some kinds of changes in the organisation of services, once the potential innovative strategies for approaching multiple risk behaviours have been determined. The commitment of cooperation by a majority plus one of all the professionals of the centre for each of the professions (administrative officers, nurses, family doctors, paediatricians and others) was required to participate in the project.

#### Recruitment process of the Health Centres and PHC professionals

The identification of the eligible centres was performed via the Medical Directors of the seven divisions of primary care services, under which the PHC of the Basque Health Service – OSAKIDETZA is organised. Four of them accepted to collaborate and they each selected two primary care centres with similar structural and population characteristics. Project presentation sessions were given to the professionals of the selected centres, in which members of the research group explained the scientific and methodological details of the project, and the work plan. Then, each of the professionals were invited to collaborate through the presentation of an informed consent form. The majority of the professionals of each profession agreed to collaborate in eight of the centres; four of them being assigned for convenience to the formative research process, and the other four forming the reference or Control Group. Finally, 130 professionals (82 in the Intervention Group and 48 in the Control Group), collaborated in the project: 46 family doctors (29 in the Intervention and 17 in the Control), 45 nurses (26 in the Intervention and 19 in the Control), 27 administrative officers (18 in the Intervention and 9 in the Control), 10 paediatricians (8 in the Intervention and 2 in the Control), 3 midwives (2 in the Intervention and 1 in the Control group) and 1 social worker (Fig 1).

**Figure 1 F1:**
[figure not shown]
**Operational organization of the formative process "Prescribe Vida Saludable" in the intervention centres**. **Note**: HC, Health Centre; GP, General Practitioner; Nur, Nurse; Ped, Paediatrician; AS, Administrative Staff; Epi, Epidemiologist; Soc, Sociologist; Psi, Psychologist. Participation in Control health centres, Beraun HC: GP (5), Nur (4), Ped (1), AS (2), Social worker (1); Markina HC: GP (5), Nur (5), AS (3); Berango HC: GP (2), Nur (2), Ped (1), AS (1); and Zurbaran HC: GP (5), Nur (8), AS (3).

#### Recruitment process of community partners

The professionals belonging to centres assigned to the realisation of the formative process (Intervention Group), were asked to identify partners and resources in their community related to the promotion of healthy lifestyles. An initial list of resources and community partners for each health centre was drawn up. The members of the research team then contacted them by letter in which they were informed of the project and invited to collaborate by attending the activities within the formative process. A total of 30 community resources or agents were contacted, of which finally 18 agreed to collaborate, belonging to following fields: company doctors (2), citizen associations (4), professionals from the educational sphere (4), from municipal organisations (6) and from sports centres or facilities (2). (Figure 1).

### Formative Research

It will entail the realisation of 12 sessions directed by external facilitators and fed with selected information (reviews of scientific evidence, selected published literature, etc.) depending on the objective of each session [see Additional File 1]. These sessions respond to different strategies for the optimisation of clinical practice: needs assessment based on audit and feedback, prioritisation of areas of improvement using consensus techniques, evidence-based education sessions, and participatory modelling of interventions, by mapping and piloting of intervention components. The sessions will have a duration of approximately 90 minutes each and will be performed at intervals of at least 3 weeks, over the course of 12 months. In each centre, a coordinator will be identified to perform the necessary organisational tasks and they will be person responsible for communication with the research team. Before each session, they will be given and will distribute to the rest of professionals a summary of the previous session and the objectives of the present one, as well as selected documentation and support materials. After the execution of the sessions, synthesis documents summarising the process undertaken, the content of the discussions, and the results achieved, will be produced. In order to guarantee the accuracy of summaries, a circulation system of these synthesis documents between collaborating professionals will be implemented, to allow verification of the validity or to effect clarifications and changes in the content, results and conclusions obtained. The 12 sessions will be organised in two stages: a descriptive one (the first 4) and a creative one (the remaining 8) [see Additional File 1].

#### Descriptive Stage

In order to prioritise areas for optimisation in healthy lifestyle promotion taking into account the real-world context of the participating health centres, a process of strategic needs assessment will be carried out followed by a process for reaching consensus. The needs assessment in each centre will be based on two sources of information. On the one hand, a transversal descriptive study of the actual practice, skills, knowledge, perceived barriers and resources in relation to healthy lifestyle promotion by health centre professionals. On the other hand, data analysis will be performed on the prevalence of risk behaviours in the population and reception of preventive practice as reported by the users at the level of the health region of each collaborating centre, the information being taken from the Health Surveys of the Basque Autonomous Region in 2002 and 2007 [47,48]. The results of the needs assessment will be presented and discussed with the professionals and the community partners of each centre to gather their opinions concerning the presented indicators, the strengths, weaknesses, opportunities and threats for the centre and community, and possible areas for optimisation.

Subsequently a process for reaching consensus will be performed to identify and prioritise areas for optimisation in healthy lifestyle promotion focused on at least two risk behaviours with high prevalence or high priority in a specific target population. For this, the Nominal Group technique [49] will be used in which, after the identification of proposals by each of the professionals of the centre and community partners involved, the prioritised selection of one area of optimisation will be undertaken through two rounds of evaluation of the proposals on the basis of four dimensions: the magnitude of the problem, significance or potential impact, vulnerability and feasibility, following the method proposed by Hanlon [50]. The area prioritised for optimisation in each centre will be the goal for healthy lifestyle promotion, the object of the creative stage for the design and modelling of feasible and sustainable interventions.

#### Creative stage

In a second stage, we will proceed to the design and participative modelling of innovative interventions for addressing and managing multiple risk behaviours that could feasibly be implemented in a sustainable way in the real context of PHC. For this, two communication sessions on the evidence relating to risk behaviour modification will be organised, supported by selected documentation derived from the reviews of the scientific literature undertaken in the preclinical phase [51]. The sessions will have the following content: a) theoretical models of healthy lifestyle modification; and b) evidence of effective intervention strategies, in which effective models and strategies for addressing and managing risk behaviours in PHC will be described.

On the basis of the theoretical models and intervention strategies described in the aforementioned sessions, professionals of the centre will perform an analysis prior to the programme planning to identify the potential specific objectives – personal, interpersonal and environmental factors that should be worked on to begin and maintain the process of behavioural and environmental change – as well as potential concrete intervention actions – strategies or measures intended to modify these aforementioned specific objectives or key factors [16-18].

The proposal presented by the professionals concerning the specific intervention objectives and strategies will be analysed, reworked, and completed by the members of the research team. Afterwards, with the objective of concluding the prior analysis of the programme, the professionals of the centre and community partners will proceed to the determination of potential strategies for translating and sustainably introducing the plan to the real-world conditions of the centre and the community. For this, the professionals of the centre and community partners potentially involved in each intervention action will be identified, as well as the necessary resources and the sequence of implementation of intervention: WHICH action is to be undertaken by WHOM, HOW, WHEN and WHERE. To facilitate this exercise, the members of the research team will produce selected documentation concerning action-research initiatives at an international level related to programmes for addressing risk behaviours in a clinical context, with the objective of serving as an example or suggesting new ways of translating research into practice, and of introducing and coordinating intervention strategies and actions.

The essential active components of the preliminary programme for healthy lifestyles promotion will be progressively piloted in the real-world conditions of the health centres for a period of between one and three months. For this, the professionals of the centre will select intervention objectives and actions to pilot on the basis of their importance in the process of behavioural change, their innovative nature or uncertainty over their true feasibility. Then, pilot loops along with their associated evaluation sessions will be undertaken. Subsequently, a structured group discussion session will be organised to analyse the real feasibility of the strategies and actions piloted, in order to optimise their potential impact and sustainable integration. With respect to these intervention strategies and actions, the key components and processes will be identified. Barriers and resources in relation to the context of each centre (personal, material or organisational) that make it easy or difficult to set the process of implementation in motion, and necessary changes and readjustments will also be identified.

On the basis of the feasibility evaluation regarding intervention actions and implementation strategies, and from the overall conclusions of the formative process undertaken in each centre, a final selection and standardisation of the following intervention programme components will be implemented: a) operational objectives of the programme; b) target population for the intervention (criteria for eligibility and exclusion) and mechanisms for addressing them; c) personal factors and characteristics (socio-demographic, biological, health status, risk status, lifestyle, beliefs and attitudes, family, etc.) essential to evaluate in order to adapt and guide the process and content of the intervention; d) key components of the intervention: strategies or processes; personnel involved; material or organisational resources needed, with respect to the context of each centre; combination of these components; and intensity of the intervention.

### Comparison Groups

The professionals of the participating centres who have been included in the Control Group will maintain the usual standard care for healthy lifestyle promotion in the Basque Health Service – OSAKIDETZA and will not be the object of any formative process or intervention.

### Evaluation

The primary outcome measure for the evaluation of the impact of the formative process will be the professionals' self-reported healthy lifestyle promotion practice, assessed through an updated version of the *Preventive Activities Questionnaire *[52]. This same instrument will be used to assess the following factors associated to healthy lifestyles promotion: attitude towards the promotion of healthy lifestyles, perceived barriers, knowledge, skills and confidence for addressing healthy lifestyles. Additionally, the organizational climate in the health centre will be assessed using a translated and culturally adapted version of the *Survey of Organizational Attributes for Primary Care (SOAPC) *[53].

The *Preventive Activities Questionnaire *[52] was originally developed in the framework of a research project whose objective was to estimate how frequently preventive activities recommended by the main consensus groups were put into practice in the PCCs of the Autonomous Region of the Basque Country. In order to update the questionnaire, a panel of five experts in health promotion was assembled from PHC professionals (family doctors and nursing personnel), epidemiologists, psychologists and sociologists. The expert panel revised the original questionnaire and suggested changes and new questions on the basis of: 1) previous experience in application of the tool, for which the authors of the questionnaire were interviewed; 2) the results of the previous formative research (preclinical phase) regarding the integration of healthy lifestyle promotion in PHC [1]; and 3) a rapid review of tools for assessing preventive practices in the context of PHC. The research team drew up a first version of the questionnaire which was then submitted to the expert panel. They were asked to evaluate: the content validity, that is, whether the items within the questionnaire were capable of evaluating all the dimensions intended to be measured; the logical order of the questions and the sections; their grammatical quality; and the adequacy of the scales for each item punctuation. The questionnaire was reedited according to the contributions given by the expert panel.

For the evaluation of the centre as an organisation and, in particular, the perception of the professionals of the organisational climate, a translated and culturally adapted version of the *SOAPC *[53] will be used. A structured process of translation and back-translation of the original version of the questionnaire was performed by two bilingual researchers independently. This process yielded two translated versions that were quantitatively evaluated by each of the members of the expert panel independently. Each member had to judge the two versions on whether concepts expressed were equivalent, their clarity and the naturalness of the style of the writing. Subsequently a consensus meeting was used to reach agreement on a unique new version of the questionnaire, which was subsequently discussed with the authors of the original questionnaire.

A piloting of the two questionnaires was undertaken with 21 professionals of the most representative professions of the health centre (4 administrative officers, 10 nurses and 7 doctors). After the pilot trial, to obtain the final version, the questionnaire was again submitted to evaluation by the expert panel, and after the analysis, some questions were rewritten and some others removed, for not returning relevant information.

The updated version of the *Preventive Activities Questionnaire *(UIAPB) is divided into 7 sections. It consists of 120 items and investigates the following dimensions: 1) attitude towards healthy lifestyle promotion in PHC; 2) current self-reported practice of healthy lifestyle promotion; 3) knowledge, skills and perceived effectiveness in addressing risk behaviours; 4) resources for healthy lifestyle promotion in the consulting room/PCC; and 5) perceived barriers to health promotion. The translated and culturally adapted version of the SOAPC comprises 19 items which measure 5 relevant organisational factors: 1) communication: ability of the professional to work in a team when problems and differences arise; 2) practice-wide decision-making: participation of the professionals of the centre in decision-making; 3) nurses' participation in decision making: participation specifically of the nursing staff in decision-making; 4) stress/chaos: workload of the professionals of the centre; and 5) history of change: history of organisational changes and/or culture within the centre.

The indicators related to the formative programme planning process to be evaluated are based on the RE-AIM model: a) Reach: percentage of participating centres, professionals and partners (among the eligible ones), and their representativeness; b) Efficacy and evaluation of the experience: impact of the formative process on healthy lifestyle promotion practice of the participating professionals and their perception concerning the usefulness of the formative process and its results; c) Adoption and implementation: degree of execution of the components of the formative process as planned: number and duration of the sessions, number of participants in each session, etc.; d) Maintenance and monitoring: degree of continuation of the formative process components and changes made; percentage of participants leaving the study, their representativeness and impact on the Reach, Adoption and Efficacy of the formative process [54].

### Analysis

In order to evaluate the changes associated with the formative process, quantitative comparisons will be performed between the professionals assigned to the Intervention Group and those from the Control Group, on an intention to treat basis. The means of continuous variables will be compared using the Student's t test and the proportions using the Chi-square test. The differences between the two groups will be estimated and the 95% confidence interval calculated. The comparisons will be adjusted for potential confounding factors by stratified analysis. Finally, multivariate statistical models, linear for continuous variables and logistic for proportions, will be constructed in order to simultaneously account for possible confounding effects, following a "forward strategy" guided by the aforementioned stratified analysis. The sample size of the present formative research study (130 health professionals, 30% in the control group) will provide a greater than 80% power to detect as significant (alpha = 0.05) a difference of at least 20% (improvements of 5% and 25% in the control and intervention groups, respectively) in the proportion of professionals that report to ask and advice about healthy lifestyles to the mayority of their patients.

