### Design

A phase I formative research [43] will be performed in four PHC centres of the Basque Health Service – OSAKIDETZA. In a first descriptive stage, a strategic needs assessment will be carried out along with the prioritisation of the areas of preventive practice to be optimised and selection of the aims of the programmes. In a second, creative stage, specific objectives of intervention will be identified based on theoretical models of behaviour change and collaborative design of specific intervention actions for addressing and managing multiple risk behaviours will be undertaken.

Within the formative research, a quasi-experimental pre-post evaluation study will be performed to compare the changes in indicators related to health promotion practice in the four PCCs assigned to the aforementioned formative research process (Intervention Group) and those of other four centres, matched in structural and population characteristics (Control group) [46]. Additionally, Nominal Groups will be performed with professionals belonging to intervention centres, in order to identify the successes, strengths, weaknesses and shortcomings of the process, as well as experiences concerning its usefulness, and difficulties and barriers with respect to the cooperation between researchers and clinicians and between professions within the centres.

The project was approved by the Institutional Primary Care Research Committee of the Basque Health Service/Osakidetza, on 12^th ^April 2007, by the Basque Country Clinical Research Ethics Committee (Ref: 06/2008), and evaluated and approved for funding by the Basque Government Department of Health (Ref: 2007111009).

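### Centres were matched within divisions, but the Analysis section does not fix the division pair in the between-group comparison and leaves it to data-guided selection

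*Protocol article*

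**What the plan says.** **Design.** The Design section compares pre-post changes in four intervention centres with "those of other four centres, matched in structural and population characteristics (Control group"). The recruitment section gives the source of the match. Of the seven divisional directors approached, "Four of them accepted to collaborate and they each selected two primary care centres with similar structural and population characteristics". Allocation was not random: "four of them being assigned for convenience to the formative research process, and the other four forming the reference or Control Group".

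**Sizes.** The recruitment section reports "130 professionals (82 in the Intervention Group and 48 in the Control Group"). The note to Figure 1 lists staff for each control centre, for example "Berango HC: GP (2), Nur (2), Ped (1), AS (1"). The sizes of the intervention centres are in the figure itself, which is not reproduced in the text reviewed.

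**Analysis.** The Analysis section states that "quantitative comparisons will be performed between the professionals assigned to the Intervention Group and those from the Control Group". Means are compared by Student's t test and proportions by chi-square. Comparisons are then adjusted for potential confounders by stratification, and linear or logistic models are built forward, guided by the stratified results. No confounder is named, and neither pair, division nor centre is mentioned.

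**The concern.** Because centres were assigned by convenience, matching within divisions is, apart from the pre-post comparison, the only protection against confounding that the design itself provides. It protects a pooled comparison only if each pair makes up the same share of both groups. If the shares differ, a division whose practice changed more than the others during the year, for example through a local programme or new management, counts more in one group than in the other. That difference then appears as part of the intervention effect.

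The factor that prevents this was known before any data were collected. Under the stated plan it is nonetheless absent from the main tests and reaches the models only if the stratified analysis and the forward selection pick it up.

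**Working it through.** **1. The plan's own power figure.** Inputs from the Analysis section: 130 professionals, 30% control (39 and 91), 5% against 25%, alpha 0.05 (two-sided assumed).

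- Pooled proportion: (39 × 0.05 + 91 × 0.25)/130 = 0.19.
- SE under no difference: √[0.19 × 0.81 × (1/39 + 1/91)] = 0.0751.
- SE under the alternative: √(0.05 × 0.95/39 + 0.25 × 0.75/91) = 0.0573.
- Power: Φ[(0.20 − 1.96 × 0.0751)/0.0573] = 82.2%.

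The stated power above 80% is reproduced for an unpaired test of independent professionals. With the actual 48 and 82 the same formula gives 86.9%.

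**2. Control shares.** From the Figure 1 note the four control centres have 5+4+1+2+1 = 13, 5+5+3 = 13, 2+2+1+1 = 6 and 5+8+3 = 16 professionals, total 48. The shares are 27.1%, 27.1%, 12.5% and 33.3%.

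**3. When pooling is safe.** Assume one centre of each division in each group. The bias in the pooled difference is

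Σ (intervention share − control share) × (mean change in that division).

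It is zero whenever the intervention-to-control ratio is the same in every pair. The overall ratio is 82/48 = 1.71, so balance needs intervention centres of about 22, 22, 10 and 28. Unequal centre size alone causes no bias.

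**4. Size of the bias.** If divisions vary independently in change with standard deviation σ, the bias has standard deviation σ × √Σ(share difference)². Its largest value is the range of division means times the sum of the positive share differences. Intervention sizes below are assumptions, listed in the order of the control centres.

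| Assumed intervention sizes | Share differences | Multiple of σ | Largest bias, 10-point range | Largest bias, 20-point range |
|---|---|---|---|---|
| 22/22/10/28 (proportional) | −0.003, −0.003, −0.003, 0.008 | 0.01 | 0.1 | 0.2 |
| 20.5 each (equal) | −0.021, −0.021, 0.125, −0.083 | 0.15 | 1.2 | 2.5 |
| 16/20/30/16 (discordant) | −0.076, −0.027, 0.241, −0.138 | 0.29 | 2.4 | 4.8 |

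For the equal case: √(0.0208² + 0.0208² + 0.125² + 0.0833²) = 0.153. Over all pairings, sizes 14, 18, 22 and 28 give multiples from 0.069 to 0.276, and sizes 12, 17, 23 and 30 give 0.075 to 0.312. In both sets the low end arises when small centres are paired with small ones.

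**5. Effect on the test.** In 20,000 simulated trials with no intervention effect and no within-centre correlation, the type I error was:

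| Assumed division improvement rates | Intervention sizes | Pooled chi-square | Stratified by pair |
|---|---|---|---|
| 10/10/25/5% | proportional | 0.045 | 0.048 |
| 10/10/25/5% | about equal | 0.055 | 0.048 |
| 10/10/25/5% | 16/20/30/16 | 0.088 | 0.047 |
| 5/10/35/5% | proportional | 0.038 | 0.049 |
| 5/10/35/5% | about equal | 0.066 | 0.048 |
| 5/10/35/5% | 16/20/30/16 | 0.166 | 0.047 |

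**6. Price of stratifying.** With 5% against 25% in every pair, power was 0.89, 0.89 and 0.87 for the three size patterns when stratified, against 0.89 pooled.

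**The case against.** The strongest reply is that no bias has been shown. The deciding intervention sizes are not readable, and centres chosen for structural similarity may well be close to proportional in staff. In that case the bias is negligible and the pooled test is even slightly conservative. This stands. A reader might infer from the unequal control centres that pair shares do differ between groups. The documents do not support that, because control sizes and a total of 82 say nothing about how the 82 are divided.

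A reader might also infer that the analysis disregards the matching altogether. That is too strong. A stratified adjustment and multivariable models are planned, division could enter either, and an article need not list every covariate. What remains is that the article does state how factors enter, by a forward strategy guided by the data, and that is the wrong route for a design factor.

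Nor does every difference between divisions distort the effect. The evaluation compares changes, so stable differences in management, population or resources largely cancel. Only differences in change over the year matter.

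Two further limits stand. One centre per division in each group is implied, not stated. Stratifying also recovers no precision, so the argument for it rests on bias, not on the standard error.

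**Conclusion.** The point holds as a weakness in how the analysis is fixed, not as a demonstrated bias. The design is matched by division; the stated tests are unpaired, and the pair is secured in no later step. The possible bias runs from about zero with proportional sizes, through 0.15 times the between-division SD of change with equal intervention centres, to about 0.3 times with discordant sizes. For an assumed SD of change of 10 points that is roughly 0, 1.5 and 3 points, which is modest against the planned 20-point difference. Type I error well above 5% appeared only when discordant sizes were combined with division improvement rates 20 to 30 points apart.

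The result rests on assumed intervention sizes, assumed spread between divisions, and one centre of each division in each group. The change is still worth making, because the remedy costs almost nothing.

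**What to change.** First confirm, and state in the text, that each division has one centre in each group. A division with both centres in the same group would contribute nothing to a stratified comparison. Then amend the Analysis section so that:

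- every between-group comparison is stratified by division pair: a Mantel-Haenszel risk difference over the four pairs for proportions, and pair as a fixed factor in the linear and logistic models;
- the pair is in every model from the start and is not a candidate in the forward selection;
- the four within-pair differences are shown beside the overall result.

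The cost is one or two sentences, three degrees of freedom in the professional-level models, and at most about two points of power in the cases examined (0.87 against 0.89). The change does not deal with correlation among professionals within the eight centres, which needs its own provision, or with remaining differences between the two centres of a pair.

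### Whole centres (4 vs 4) receive the intervention, but the stated tests and power treat 130 professionals as independent, so standard errors and 95% intervals are too small if outcomes correlate within centres

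*Protocol article*

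**What the plan says.** The Eligibility criteria section states that "the intervention unit is the PCC". The section on recruitment of centres and professionals reports eight centres, "four of them being assigned for convenience to the formative research process, and the other four forming the reference or Control Group", and "130 professionals (82 in the Intervention Group and 48 in the Control Group"). The Formative Research and Descriptive Stage sections organise the sessions, the coordinator, the needs assessment and the single prioritised area by centre.

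The Analysis section compares the professionals of the two groups: "The means of continuous variables will be compared using the Student's t test and the proportions using the Chi-square test". It adds 95% confidence intervals, stratified analysis and "multivariate statistical models, linear for continuous variables and logistic for proportions", built to deal with confounding. The power statement rests on "130 health professionals, 30% in the control group" and claims more than 80% power for improvements of 5% and 25%.

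The article nowhere mentions clustering, an intraclass correlation, a design effect, a random or robust centre term, or a centre-level summary.

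**The concern.** The t test, the chi-square test and ordinary linear and logistic regression all assume independent observations. Professionals in one centre work in the same organisation and go through the same programme together, or none, so their changes are likely to be correlated. For the organisational climate survey (SOAPC), which the Evaluation section uses to assess the centre as an organisation, some correlation is almost built in.

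The planned adjustment does not help. It is aimed at confounding, not at correlated errors, and centre cannot enter as an ordinary fixed covariate because it is nested within group. A chance difference between four centres and four others could therefore be reported as an effect of the formative process, on the primary outcome and on every secondary comparison. The programme is phase I of a staged framework, so a false lead could carry into later phases.

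**Working it through.** **Inputs.** Group sizes are 48 and 82 (recruitment section). Control centre sizes come from the note to Figure 1; the first reads "GP (5), Nur (4), Ped (1), AS (2), Social worker (1"), which is 13, and the four are 13, 13, 6 and 16 (sum 48). Intervention centre sizes are not visible, so 21, 21, 20 and 20 are assumed (sum 82). The ICC is not in the document and is varied. It means the ICC of the analysed outcome, here change. Alpha is taken as two-sided 0.05.

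**Step 1: reproduce the stated power.** Take professionals as independent, with 30% of 130 = 39 controls and 91 intervention.
- Pooled proportion = (39×0.05 + 91×0.25)/130 = 0.19.
- Null SE = √[0.19×0.81×(1/39 + 1/91)] = 0.0751.
- Alternative SE = √[0.0475/39 + 0.1875/91] = 0.0573.
- Power = Φ[(0.20 − 1.96×0.0751)/0.0573] = Φ(0.92) = 82.2%.

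With the actual 48/82 the same formula gives 86.9%. The claim of over 80% is thus met by a standard individual-level calculation with no design effect.

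**Step 2: design effect.** Per group, DEFF = 1 + (Σm²/Σm − 1)×ICC.
- Control: Σm² = 169 + 169 + 36 + 256 = 630, and 630/48 = 13.125, so DEFF = 1 + 12.125×ICC.
- Intervention: Σm² = 441 + 441 + 400 + 400 = 1682, and 1682/82 = 20.51, so DEFF = 1 + 19.51×ICC.
- For the difference: (DEFF_control/48 + DEFF_intervention/82)/(1/48 + 1/82) = 1 + 14.85×ICC.

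**Step 3: type I error of the planned test.** The approximation is 2×[1 − Φ(1.96/√DEFF)]. At ICC 0.05, DEFF = 1.74, 1.96/1.32 = 1.48, and the result is 13.8%. The interval-width column is √DEFF × 2.447/1.96, where 2.447 is the 97.5% point of t on 6 df.

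| ICC (assumed) | DEFF | Type I, formula | Type I, simulated chi-square | Correct 95% CI width ÷ planned (6 df) |
|---|---|---|---|---|
| 0.01 | 1.15 | 6.7% | 6.6% | 1.34 |
| 0.02 | 1.30 | 8.5% | 8.4% | 1.42 |
| 0.05 | 1.74 | 13.8% | 13.6% | 1.65 |
| 0.10 | 2.49 | 21.4% | 21.6% | 1.97 |
| 0.15 | 3.23 | 27.5% | 27.9% | 2.24 |

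The simulation draws beta-binomial centre effects under no difference, with an event rate of 17.6%. A t test on the eight centre results (6 df) keeps about 4.3% to 5.4% throughout.

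**Step 4: power for 5% vs 25% on 6 df, 48/82.** SE = √[0.0475×DEFF_control/48 + 0.1875×DEFF_intervention/82]. At ICC 0.05 this is 0.0781, so the noncentrality is 0.20/0.0781 = 2.56, and power against the critical value 2.447 is 57%. The same formula gives 77% at ICC 0.01, 71% at 0.02 and 43% at 0.10. Simulating the unweighted centre-level t test gives about 76%, 71%, 59% and 46% at ICC 0.01, 0.02, 0.05 and 0.10.

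**The case against.** The strongest reply concerns size, not principle. A reader might infer one headline figure, for instance that false positives are three to four times nominal. The document does not support that. From DEFF = 1 + 14.85×ICC, a type I error of 15% to 20% needs an ICC of about 0.057 to 0.090, and no ICC is given. At 0.01 to 0.02 the inflation is only 1.3 to 1.7 times.

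The design is also pre-post. Stable differences between centres partly cancel in change scores, so the relevant ICC may be smaller than that of a single survey. This stands as a reason for caution about size, but change scores do not make colleagues independent.

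A reader might also take 6 degrees of freedom as settled. It is not. The Design section calls the control centres matched, and four service divisions each chose two similar centres. If each pair was split between the groups, which is not stated outright, a paired analysis would have 3 df. Neither version comes near the 128 df (130 − 2) of the planned t test.

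Finally, this is formative research, and the group comparison serves the second of two objectives. That limits the consequences but does not justify an analysis that contradicts the declared unit. Nor is this detail left to an unseen analysis plan: the article names its tests, models and power basis.

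**Conclusion.** Wrong as written, and it should be corrected. The conflict between the declared intervention unit and the stated tests follows from the text alone. That standard errors and intervals are too small follows for any positive within-centre correlation of the outcome. That such correlation exists is very plausible, but it is not shown in the document.

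The size is conditional: roughly 7% to 28% type I error for an ICC of 0.01 to 0.15, with intervention centre sizes assumed near 20 to 21. No single multiple should be quoted as the error rate of this study. The statement of more than 80% power does not hold on 6 df even at ICC 0.01.

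A reader might also infer that a corrected test would let a difference be credited to the formative process. It would not. The centres were placed in groups by convenience, and the corrected analysis deals with sampling error between centres only.

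**What to change.** In the Analysis section, replace the professional-level tests as the primary comparison by one of two options, chosen in advance:
- **Centre-level summaries.** Compute each centre's mean change or change in proportion (covariate-adjusted where adjustment is planned) and compare four with four by a t test on 6 df. If each matched pair was split between the groups, use a paired test on 3 df and say so.
- **Mixed model.** Fit professionals with a random centre effect and a small-sample degrees-of-freedom correction. Uncorrected robust standard errors are not reliable with eight centres.

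Report the observed ICC. State how the centre pairs were assigned. Restate the power for the chosen analysis over an assumed ICC range. For 5% vs 25% on 6 df it is about 75-77% at ICC 0.01, 70-71% at 0.02 and 57-59% at 0.05; a paired analysis needs its own figure. Keep the convenience assignment as a stated limitation.

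The cost is rewording and a little more analysis, with no new data. The downside is wider intervals and a less favourable stated power.
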